### PCMT - weekly intervention schedule

To make training easily accessible to the participants at the worksite, a weekly training structure of 20 min. supervised physical training is available four times per week (Monday, Tuesday, Thursday and Friday) with 3 session possibilities daily (10.00 am, 10.30 am and 11.00 am). Mindfulness is available once weekly (Wednesday) on two separate occasions (10.00 am and 11.00 am). All instructors are available for consultation and support via email throughout the intervention weeks and participants are encouraged to train and practice mindfulness during leisure time. Instructors take attendance to physical training- and mindfulness classes and monitors non-participation rates for each participant.

### PCMT - adjusting the strength training element

In case of acute worsening of pain or other contraindications during the time of physical training, the training instructor applies the following 4-stage model, previously described by our research team [57], to adjust the specific exercise.

*Stage 1*: Reduce loading intensity. A reduction in load (e.g. resistance of elastic tubing) should be implemented in the specific exercise that causes an increase in acute pain in the back, neck, shoulder, elbow or hand. A load reduction of up to 100% can be necessary, i.e. performing the movement without external resistance.

*Stage 2*: Reduced movement velocity. If a reduction in load fails to address the problem the movement velocity should be reduced.

*Stage 3*: Reduced range of motion (ROM). As a final action to solve the problem, the ROM should be reduced the point where pain is not worsened.

*Stage 4*: Exercise termination. If none of the above stages resolves the problem, the specific exercise will be terminated and replaced by a targeted joint mobility or motor control exercise.

Progression in strength and motor control training is done in reverse, i.e. increasing ROM, increasing movement velocity and increasing the load by applying external resistance. The progression, as well as the regression is supervised and controlled by the instructor present.

### REF group

The participants of the REF group receive an email with encouragements to participate in the company’s on-going initiatives, e.g. weekly elastic band group training sessions (only available in some departments) and are encouraged to continue to take “exercise breaks” whenever needed. As this is part of the existing and on-going program at the company, it can be considered “usual care”. No new interventions are added for the REF group.

### Compliance, adherence and dropouts

Compliance, adherence to training and dropouts will be tracked and reported in the main article on the primary outcome of pain. PCMT instructors will keep track of all participants for each training session and send out weekly information emails reminding the participants to prioritize the training and mindfulness sessions. Apart from increasing compliance, this procedure also eliminates any potential REF group participants finding their way to the training and mindfulness sessions, thus reducing the likelihood of cross contamination significantly.

### Co-interventions

Participants of both groups are recommended to continue their usual physical activities alongside the intervention. The company’s own health and safety professionals are available to provide ergonomic education in accordance with the standard company policy, which consists of ergonomic worksite observations by trained professionals and subsequent individualized recommendations on changing task-specific positions and adjusting ergonomic aids to fit each department structure. Each individual department management is responsible for prioritizing and utilizing the option of ergonomic support, thus making it voluntary. This is part of the existing company policy on ergonomic guidance and is equally available to all participants of both groups.

In this study, co-interventions are tracked as follows (i.e. asked by questionnaire at baseline and follow-up): 1) number of days using pain medication (typical over-the-counter pain medications, i.e. acetaminophen/paracetamol and NSAIDs) within the last week, 2) number of treatment sessions (e.g. by a medical doctor or physical therapist) for pain in the back, neck, shoulders, elbows or hands/wrists within the last month. The baseline information about this will be added to the article reporting the primary outcome, together with the follow-up results.

### Primary outcome measure

Our primary outcome measure is change in average pain intensity (lower back, upper back, neck, shoulders, elbows and hands/wrists) by questionnaire (scale 0-10) from baseline to week 10. The analysis will be adjusted for pain intensity at baseline. The regions of the body will be defined by drawings from the Nordic Questionnaire [58].

### Secondary outcome measure

Stress is measured from baseline to week 10 by Cohen’s perceived stress scale which is based on the answers of 10 questions each scored with the following categories: i) Never, ii) Almost never, iii) Sometimes, iv) Fairly often and v) Very often. Examples of questions include: *“In the past month, how often have you found that you could not cope with all the things you had to do?”* and *“In the past month, how often have you been able to control irritations in your life?”*[59].

### Other outcome measures

#### Work ability

Work ability is assessed by the Work Ability Index questionnaire [60, 61] from baseline to 10 week follow-up and cognitive performance is assessed by CNS Vital Signs [62] at baseline and follow-up. Electroencephalography (EEG) will be used to sample brain activity during the CNS Vital Signs test.

All outcome measures will be collected by trained clinical examiners and by questionnaire survey at baseline and after the 10-week intervention period.

#### Fear avoidance

Fear avoidance is evaluated by the Fear Avoidance Beliefs questionnaire (FABQ) by Waddell et al. [63] at baseline and follow-up. Briefly, the FABQ is a two-part questionnaire. The first part consists of five questions/statements about pain and physical activity and the second part consists of 11 questions/statements about how work affects the participants’ perception of pain. Each question is scored from 0-5 ranging from completely disagree (0) to completely agree (5).

#### Muscle function

Muscle strength, function and tenderness of the shoulder, arm, wrist/hand is assessed by maximal isometric voluntary contractions in a custom-built dynamometer (Bofors Elektronik, Karlskoga, Sweden) setting and by pressure-pain threshold testing (PPT) [64]. Also rate of force development (RFD), force steadiness (FS), force precision (FP) and fatigue (F) are measured by using custom-made MATLAB programs. The strength tests are a part of an extensive physical examination by trained (and blinded) medical professionals at baseline and follow-up. Muscle activation level is measured by surface electromyography (EMG) (Nexus Mark 10, Mindmedia, Netherlands) on the forearm extensors, shoulder external rotator (Infraspinatus Mm.) and descending part of the trapezius muscle. Further, surface EEG (Nexus Mark 10, Mindmedia, Netherlands) will measure global brain activity during pre- and post testing by using a single a single sensor placement on the forehead (Fpz) [65].

### Sample size and power

A priori power analysis based on previous measurements reveals that 27 participants of each group for 95% power, type I error probability of 5%, SD of 1.5 and a minimal relevant difference in pain intensity of 1.5 is sufficient to test the null-hypothesis of equality (alpha = 0.05, beta = 0.05). With an estimate of a 10% dropout during the intervention period, the minimal group size should be 30 (i.e. a total of 60 participants).

### Statistical analysis

All statistical analyses will be performed using the SAS statistical software for Windows (SAS Institute, Cary, NC). The change in perceived pain (0–10 scale) will be evaluated using a repeated measures linear mixed model with *group*, *time* and *group by time* interaction as independent variables. Subject is entered as a random effect. Analyses will be adjusted for baseline values. We will perform all statistical analyses in accordance with the intention-to-treat principle using the Proc Mixed procedure of SAS, which inherently accounts for missing values. An alpha level of <0.05 will be accepted as significant. Outcomes will be reported as between-group, least mean square differences and 95% confidence intervals from baseline to follow-up.

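### The primary mixed model, as worded, uses baseline pain as both response and covariate, so the promised baseline adjustment has no effect on the group-by-time estimate and the standard error can be too small

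*Protocol article*

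**What the plan says.** The Primary outcome measure section defines the endpoint as change in average pain over the body regions, "by questionnaire (scale 0-10) from baseline to week 10", and adds: "The analysis will be adjusted for pain intensity at baseline". Under Other outcome measures (Work ability), all outcomes are collected "by questionnaire survey at baseline and after the 10-week intervention period". The Trial design section also schedules a 1-year follow-up, but the primary comparison stops at week 10.

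The Statistical analysis section evaluates the change in pain with a "repeated measures linear mixed model with *group*, *time* and *group by time* interaction as independent variables". It continues: "Subject is entered as a random effect. Analyses will be adjusted for baseline values". Results are to be reported as between-group differences in least-squares means, with 95% confidence intervals, over the interval from baseline to follow-up. No baseline-by-time term, constraint on the baseline means or covariance structure other than the random subject effect is mentioned.

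**The concern.** With two occasions, the listed terms decide what the response must be. If week 10 were the only response, time would have one level, group by time could not be estimated, and the subject effect could not be separated from the residual. So baseline must be a response, and the adjustment then makes it a covariate as well.

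Two things are at stake for the confirmatory test. The adjustment promised in two sections may not reach the reported contrast, so the precision it should bring is lost. The standard error may also be misstated, because a covariate identical to one of the responses distorts the split between between-subject and within-subject variance. No other model is given, so stress and the remaining outcomes would inherit the problem.

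**Working it through.** **Inputs.** From Sample size and power: SD 1.5, difference 1.5, two-sided alpha 0.05, 95% power, 27 per group, 30 after 10% dropout. The article gives neither the baseline-to-week-10 correlation ρ nor SDs by visit, so both are assumed and varied.

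**The plan's own figure.** 2(1.960 + 1.645)² × (1.5/1.5)² = 25.99, i.e. 26 per group by the normal approximation. The noncentral t gives 27 (power 95.0%), and 27/0.9 = 30. The sample size reproduces and is not affected by this point.

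**Step 1: the estimate.** Write D = week 10 − baseline and S = week 10 + baseline for each participant. A covariate that is constant over time enters only the S part. Group by time is estimated from D, so with complete data it equals the raw difference in mean change whether or not the covariate is present. In one fitted example it was −1.3338 both ways. With about 10% of follow-up values missing, it moved by only 0.01 to 0.04 in three examples.

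**Step 2: lost precision.** With SDs s0 (baseline) and s1 (week 10):
- Var(D) = s0² + s1² − 2ρ·s0·s1
- residual variance of ANCOVA = s1²(1 − ρ²)

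At equal SDs the ratio is (1 − ρ²)/[2(1 − ρ)] = (1 + ρ)/2, i.e. 0.65/0.75/0.85 at ρ = 0.3/0.5/0.7. The gain is smaller if s1 exceeds s0. With SDs 1.5 and 2.0 at ρ = 0.3 it is 3.64/4.45 = 0.82.

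**Step 3: the standard error.** Given baseline, the residual variance of S is s1²(1 − ρ²). This falls short of Var(D) by (s0 − ρ·s1)², which is never negative. The subject variance implied by the model is therefore −(s0 − ρ·s1)²/4. When the estimate is held at zero, the two parts are pooled, and the variance used for group by time is its correct value times

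k = 1 − (s0 − ρ·s1)²/[2·Var(D)],

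which at equal SDs is (3 + ρ)/4. Approximate type I error is 2[1 − Φ(1.96√k)].

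Worked case, equal SDs and ρ = 0.5: k = 0.875, √k = 0.935, 1.96 × 0.935 = 1.833, type I error 6.7%.

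| Assumed SDs, baseline / week 10 | √k at ρ = 0.3/0.5/0.7 | Formula, % | Simulated, 30 per arm, % |
|---|---|---|---|
| 1.5 / 1.5 | 0.908/0.935/0.962 | 7.5/6.7/5.9 | 7.2/6.5/6.2 |
| 1.5 / 2.0 | 0.953/0.981/0.999 | 6.2/5.5/5.0 | 6.1/5.7/4.9 |
| 1.0 / 1.5 | 0.967/0.991/0.999 | 5.8/5.2/5.0 | 6.0/5.2/5.4 |
| 1.5 / 1.2 | 0.867/0.886/0.902 | 8.9/8.2/7.7 | 8.8/8.1/7.7 |

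The formula assumes that the bound is reached. At equal SDs it is reached in about 98–100% of simulated trials. In the two rows with the larger week-10 SD it is reached in only about 34–39% at ρ = 0.7, where s0 and ρ·s1 nearly coincide. ANCOVA held about 5% throughout.

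**Scale.** At 27 per group, equal SDs and ρ = 0.5, the model as worded reports a mean standard error of 0.380 where the true value is 0.406. ANCOVA reports 0.355 where the true value is 0.356.

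**The case against.** The double use is inferred. The article says that analyses are adjusted for baseline but not how baseline enters, and an article may leave the exact model statement to an analysis plan. Some implementations that fit the words are sound. A baseline-by-time term alongside the covariate returns the ANCOVA estimate with two visits and complete data, and its type I error was 4.7–5.6% in simulation. A common baseline mean for the two arms would also work. One could also take week 10 and the 1-year visit as responses with baseline as covariate, although that sits poorly with a contrast defined from baseline to follow-up.

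This part stands: a reader might infer that no reading of the section gives a valid analysis, and the documents do not support that. What remains is that the article states none of these devices, while the terms it does state lead to the double use.

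A reader might also look at a covariate-adjusted week-10 difference from the same model and infer a much larger error rate. The plan does not name that contrast; it names change from baseline to follow-up, so the group-by-time test is the relevant one.

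Nor does it follow that the primary p-value will be anti-conservative. That depends on ρ, on the ratio of the SDs and on bounding the subject variance at zero. An unbounded subject variance gives the correct change-score standard error. Because entry requires pain of at least 3 in some region, a baseline SD below the week-10 SD is plausible, and the excess is then small. The estimate itself is unbiased under randomisation.

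**Conclusion.** The point holds as a should-fix. On the plain reading, and with complete data, the baseline adjustment has no effect on the primary estimate, whatever ρ, the SDs or the variance bound. The cost in precision is certain in direction but not in size: ANCOVA needs 65–85% of the change-score variance at equal SDs and ρ of 0.3–0.7, with less to gain if the week-10 SD is larger.

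The understated standard error is a possibility, not a certainty. Under a zero bound, type I error is about 6–7% at equal SDs, 5–6% with a larger week-10 SD and 8–9% with a smaller one (1.2 against 1.5). All SDs by visit and all correlations are assumptions.

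**What to change.** Use baseline once and say how. Either of these does it:
- **ANCOVA:** week-10 average pain on group with baseline pain as covariate, one record per participant, no time term and no random subject effect.
- **Constrained longitudinal model:** baseline and week 10 as responses, a common baseline mean for both arms, unstructured covariance and no baseline covariate.

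In both, name the week-10 group contrast as the primary estimate. Word the Primary outcome measure and Statistical analysis sections identically, and apply the same model to stress and the other outcomes. The cost is a few lines of text and SAS code, settled before unblinding; no further data or participants are needed.

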The link between musculoskeletal pain and situational stress should also be taken into account [35]. Stress can have widespread effects on emotional, physical, cognitive and behavioural wellbeing. Typical symptoms of stress include frustration, fatigue, headaches, chest pain and rapid heartbeat, forgetfulness, disorganization, and tense muscles [36–38]. Importantly, a recent prospective cohort study showed that high muscle tension was associated with almost 4-fold increased chance of developing neck pain 1 year later [39]. The symptoms of stress are similar to how CFS is defined by the Centers for Disease Control and Prevention (CDCP), who defines it as *“a complex illness characterized by prolonged debilitating fatigue and multiple non-specific symptoms including headaches, re- current sore throats, fever, muscle and joint pain, and neurocognitive complaints”*[34]. Based on psychological research a biopsychosocial intervention strategy aimed at reducing musculoskeletal pain by taking fatigue and situational stress into account seems appropriate to investigate, as psychosomatic research shows an isomorphic- (same time increases in pain lead to same time increases in stress and vice versa), consequence- (increases in pain precede increases in stress), and a precursor (increases in stress precede increases in pain) stress-pain relationship [35]. This supports a psychological theory of using individually tailored multifactorial interventions in chronic pain rehabilitation settings.

The aim of this study is therefore to investigate the effect of an individually tailored biopsychosocial intervention strategy versus company policy ergonomics and on-going exercise initiatives on chronic musculoskeletal pain, stress and work disability in lab technicians with a history of work-related musculoskeletal pain.

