### Participant recruitment

A recruitment questionnaire on musculoskeletal pain, stress and work disability are sent out to 752 laboratory technicians in a division of a large pharmaceutical company in Denmark. Based on previous work [13, 40] we conservatively estimate a recruitment level of 10-15% or 75-110 participants with chronic musculoskeletal pain. The participants must be, at the time of enrolment, suffering from chronic musculoskeletal pain in one or more of the following regions: i) upper back, ii) lower back iii) neck, iv) shoulders, v) elbows or vi) hands/wrists to participate in the study. To fulfil the definition of chronic pain all following criteria must be met for at least one of these body regions: i) pain intensity of ≥3 (0-10 Visual Analogue Scale) during the last week, ii) pain frequency of ≥3 days during the last week, iii) the pain should have lasted at least 3 months.

We will not exclude participants due to disease unless contraindications for all elements of the intervention exist. Instead, participants with typical exclusion criteria, e.g. severe hypertension, are allowed to participate in the less strenuous part of the intervention if their own doctor clears them. Thus, special emphasis of the individually tailored intervention will be to offer interventions for all employees with chronic musculoskeletal pain unless contraindications exist. Life-threatening disease and pregnancy are considered contraindications to the testing and training and we will therefore exclude such participants. Finally, stress, as measured by Cohen´s perceived stress questionnaire is not an inclusion criteria, thus participants can participate regardless of their stress level.

We will describe baseline demographics and important variables in the main article reporting results on the primary outcome. These include: i) age, ii) height, iii) weight, iv) BMI, v) pain intensity, vi) pain frequency, vii) pain duration since onset, and viii) prescription medicine, ix) other treatment modalities (e.g. by a doctor or physical therapist), x) Cohen’s stress score.

All participants will be informed about the purpose and content of the project and must provide their written informed consent to participate in the study. All experimental conditions conform to The Declaration of Helsinki.

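### The pain analysis is valid but names only baseline pain as a covariate; prespecifying the baseline perceived-stress score as well would probably gain a little precision

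*Protocol article*

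**What the plan says.** The Statistical analysis section of the protocol article plans a linear mixed model with group, time and their interaction, subject as a random effect, and results reported as between-group differences from baseline to follow-up. On covariates it says "Analyses will be adjusted for baseline values". The Primary outcome measure section makes this concrete for pain: the adjustment is for baseline pain intensity. Neither section names a further covariate.

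Other data are in hand by then. Under Participant recruitment, "A recruitment questionnaire on musculoskeletal pain, stress and work disability are sent out to 752 laboratory technicians", and Cohen's stress score is listed among the variables to be described at baseline. Under Other outcome measures (Work ability), outcomes are collected by examiners and "by questionnaire survey at baseline and after the 10-week intervention period". The Randomization section says participants are told their group by email after baseline data have been acquired.

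The Background (Fatigue and stress) describes, among other links between the two, "a precursor (increases in stress precede increases in pain) stress-pain relationship".

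**The concern.** On the plan's own reasoning, stress is a candidate predictor of later pain. It is measured in everyone before participants know their group, but the pain model does not use it. Adjusting a randomised comparison for a prespecified baseline variable introduces no bias. It removes whatever outcome variance that variable explains beyond baseline pain, and it corrects for chance imbalance.

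Chance imbalance is not remote here, because the Randomization section mentions no stratification. With 27 per group the standard error of a standardised baseline difference is √(2/27) = 0.272. A stress difference of 0.3 SD or more, in either direction, corresponds to |z| ≥ 0.3/0.272 = 1.10, which has a probability of about 27%. If an imbalance is noticed afterwards, a prespecified adjustment is easier to defend than one chosen once the data are known.

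At stake is the width of the interval for the primary estimate, not its validity.

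**Working it through.** **1. The plan's own figure.** The Sample size and power section gives "27 participants of each group for 95% power" with "SD of 1.5 and a minimal relevant difference in pain intensity of 1.5", "sufficient to test the null-hypothesis of equality (alpha = 0.05, beta = 0.05"). Sidedness is not stated; a test of equality is read as two-sided.

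- Normal approximation: 2 × (1.960 + 1.645)² × 1.5²/1.5² = 25.99, so 26 per group.
- Noncentral t: power is 0.9424 at 26 and 0.9501 at 27, so 27 per group.
- Dropout: 27/(1 − 0.10) = 30 per group, 60 in total.

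The stated figures reproduce without any extra covariate.

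**2. Gain from stress alone.** Let p be the partial correlation of baseline stress with week-10 pain given baseline pain. The article gives no value, so p is an assumption. The residual variance is multiplied by 1 − p². With n = 27 per group and k covariates,

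half-width = t(0.975; 2n − 2 − k) × SD × √(1 − R²) × √(2/n).

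The article does not say whether the SD of 1.5 is raw, of change, or residual. Here it is taken as the residual SD after baseline pain, so R² counts only what stress adds. The ratio in the last column does not depend on that choice.

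| Model | p | Half-width | Ratio to baseline pain only |
|---|---|---|---|
| Baseline pain only (t = 2.0076) | – | 0.820 | 1 |
| Plus stress (t = 2.0086) | 0 | 0.820 | 1.0005 |
| Plus stress | 0.1 | 0.816 | 0.995 |
| Plus stress | 0.2 | 0.803 | 0.980 |
| Plus stress | 0.3 | 0.782 | 0.954 |

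Example at p = 0.2: 2.0086 × 1.5 × √0.96 × √(2/27) = 0.803, which is 2.0% narrower. At p = 0.3 it is 4.6% narrower. With two added covariates that carry nothing, the ratio is 2.0096/2.0076 = 1.001, or 0.1% wider.

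**3. If a separate recruitment pain score exists.** Let both pain scores correlate r with week-10 pain and c with each other. Then R² = r² with one score and 2r²/(1 + c) with two. The remaining variance is again multiplied by 1 − p² for stress. All three values are assumed.

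- Central case r = 0.5, c = 0.7, p = 0.2, with 1.5 as the raw SD: R² rises from 0.250 to 1 − (1 − 0.294) × 0.96 = 0.322. The half-width falls from 0.710 to 0.675, about 5% narrower.
- Low end (r = 0.4, c = 0.8, p = 0): 0.751 to 0.744, 1% narrower.
- High end (r = 0.6, c = 0.6, p = 0.2): 0.656 to 0.596, 9% narrower.

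**4. How the covariate must enter.** The planned model can be read with baseline pain as a response row. The group-by-time contrast then compares the groups' within-person changes. A stress main effect adds the same amount to a person's baseline and week-10 values, so it cancels in the change. In 60 simulated complete-data trials of 27 per arm, adding recruitment pain and stress as main effects left the estimate unchanged and gave a standard-error ratio of 1.0000. The gains in steps 2 and 3 arise only if the covariate predicts week-10 pain, through ANCOVA or a covariate-by-time term.

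**The case against.** **Baseline pain is a standard and sufficient choice, and further covariates belong in an analysis plan.** The first half stands. Adjusting for baseline pain is sound, and a statistical analysis plan that is not shown may say more. But the article states the adjustment in two places, so what it states can be commented on as an efficiency point.

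**Nothing is rescued by it.** The design has 95% power at 27 per group, and 75-110 participants are expected against 60 required. This stands and keeps the point minor. It does not make precision irrelevant, because confidence intervals will be reported and the true effect may be smaller than 1.5 points.

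**Stress may add nothing once baseline pain is in the model.** The Background also describes simultaneous rises in stress and pain, which would make stress partly redundant. This stands: the gain can be nil.

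**Stronger readings.** A reader might infer that the plan discards a second pain score and that its interval is therefore 6-9% too wide. The article does not support that.

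- The section on the individualized treatment model refers to a baseline questionnaire and then to a screening questionnaire, both covering pain and stress. It does not say whether they are separate occasions. If they are one, there is no second score.
- The 6-9% comes from setting c equal to r, at values of 0.5-0.7. Two pre-allocation reports are likely to be closer to each other than to week 10. At r = 0.5 the narrowing from the second score, before the degree-of-freedom loss, is 5.7% at c = 0.5, 3.0% at c = 0.7 and 1.9% at c = 0.8. With correlations with week 10 of 0.6 (baseline) and 0.48 (recruitment), and 0.8 between the two scores, it is zero, because 0.48 − 0.6 × 0.8 = 0.

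A reader might also infer bias or lost power. Neither follows.

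**Conclusion.** The point holds as a minor, optional improvement. The primary analysis is valid under randomisation and the stated sample size is correct. Naming only baseline pain probably gives up a small amount of precision, because a stress score that the plan itself links to later pain is already in hand.

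The size is conditional throughout. From stress alone the interval would be about 2% narrower at a partial correlation of 0.2 and under 5% narrower at 0.3. With a genuinely separate recruitment pain score as well, it would be about 5% narrower, with 1-9% over r of 0.4-0.6, c of 0.6-0.8 and p of 0-0.2. It may be nil. The opposite risk is about 0.1% of width if two added covariates carry nothing. These figures assume complete data on 27 per group and covariates that enter as predictors of week-10 pain.

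**What to change.** In the Statistical analysis section, before unblinding, name baseline average pain and baseline perceived-stress score as the covariates of the primary pain analysis, and state how they enter. One option is ANCOVA with week-10 pain as the response. If baseline pain stays in the outcome vector, the alternative is a stress-by-time term, since a stress main effect alone does not change the group-by-time contrast.

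Say also whether the screening and baseline questionnaires are the same occasion. Add recruitment-questionnaire average pain as a further predictor only if they are separate.

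The cost is a sentence or two and one or two degrees of freedom out of about 50. No new data, visits or participants are needed, and the sample size and stated power stay as they are.
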